### Participants

The source population includes patients living in Canada who have a regular family physician. All patients rostered with participating family physicians are eligible for participation provided they fit inclusion and exclusion criteria.

Patients meeting the following criteria will be eligible for the trial:
Aged 70 years of age or olderTaking 5 or more long-term prescribed medications (excluding topical products) [7]Rostered to a family physician participating in the trialWilling to try discontinuation

Patient will be excluded based on the following exclusion criteria:
Unable to understand English or do not have cognitive skills to understand and respond to rating scalesTerminal illness or other circumstance precluding the 6-month study period follow-upHad a comprehensive medication review within the past 12 months

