### Sample size

Sample size calculations for the RCT were performed by the team biostatistician (LT). We used data from our feasibility study to estimate sample size: mean number of medications of 7.7, a post-intervention reduction in mean (standard deviation) of 4.2 (± 2.5). There was consensus from the expert international polypharmacy advisory group that a mean reduction of 2 medications is clinically important [42].

A sample size of at least 160 per group is sufficient to detect a difference in mean number of medications of 2, assuming a starting mean of 7 and a static control group (power set at 80%, significance level 5%). It will also allow detection of an absolute difference in the proportion of patients with drug-related side effects of 15% (10% versus 25%) and provides adequate power for subgroup analysis for the primary outcome if proportions are 40% or more. Allowance has been made for 10% attrition; therefore, the final minimum recruitment target is 180 per group (total *N* = 360).

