### Quantitative data analysis

The analysis and reporting of the results will follow the CONSORT guideline [71]. The process of patient selection and flow throughout the study will be summarized using a flow diagram. The analysis results of patient characteristics and baseline outcome variables (both primary and secondary) will be summarized using descriptive summary measures: expressed as mean (standard deviation) or median (minimum, maximum) for continuous variables depending on the distribution, and the number (percent) for categorical variables [72]. We will adopt an intention-to-treat (ITT) principle as our primary approach to analyze all outcomes and the people doing the analysis will be blind to study group allocation. Assuming data will be missing at random (MAR), we will also use multiple imputation [MI] through chained equations to impute missing data [73]. In total, five datasets will be imputed and pooled effect estimates (odds ratios for categorical outcomes, mean difference for continuous outcomes, and rate ratio for count outcomes) along with 95% confidence intervals and the associated *p* values will be reported. All statistical tests will be two-sided at the 0.05 level of significance. *P* values will be reported to three decimal places with values less than 0.001, reported as < 0.001. We will not adjust this for multiple analyses for secondary outcomes as we are considering them simply as exploratory. The patient will be the unit of analysis. Adopting an ITT principle, we will use linear regression to analyze both primary and secondary continuous outcomes. Analysis will be blinded. For categorical outcomes, we will use logistic regression. Count data models (e.g., Poisson/negative binomial regression, zero-inflated models) will be used to analyze the count outcomes. We will perform pre-specified subgroup analyses by adding an interaction term between intervention groups and the following subgroups: (1) age (≥ 85 versus < 85 years); and (2) frailty (frail versus severely frail, based on Rolfson et al., 2006 [60]). The interaction tests will be completely exploratory in nature and not adjusted for multiple testing. We examined articles in our review of reviews [74] of interventions to address polypharmacy in older adults living with multimorbidity that may have contained sub-analyses for age and frailty. We found one systematic review that contained a sub-analysis for mortality associated with deprescribing intervention subgroup analyses based on age [75]; and concluded there was no effect. Thus, we hypothesize that there will be no significant interaction effects for either sub-analysis. The interaction tests will be exploratory in nature and not adjusted for multiple testing. We will run sensitivity analyses to assess the robustness of the primary results, adopting a per-protocol approach. All analyses will be performed using SAS software 9.4 (Cary, NC).

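### The pre-specified frailty subgroup has no level for participants who are not frail, and the subgroup power sentence does not say whether it covers the planned interaction test

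*Protocol article*

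**What the plan says.** The Quantitative data analysis section plans "pre-specified subgroup analyses by adding an interaction term between intervention groups and the following subgroups". The two subgroups are "age (≥ 85 versus < 85 years" and "frailty (frail versus severely frail", the latter based on a cited frailty instrument. The section labels these tests clearly: "The interaction tests will be completely exploratory in nature and not adjusted for multiple testing". It also states an expectation: "we hypothesize that there will be no significant interaction effects for either sub-analysis".

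The Participants section sets the entry rule. It begins "Aged 70 years of age or olderTaking 5 or more long-term prescribed medications", and adds rostering to a participating physician and willingness to try discontinuation. The exclusions are language or cognitive barriers, terminal illness or another obstacle to follow-up, and a recent comprehensive medication review. Frailty appears in neither list, and "All patients rostered with participating family physicians are eligible for participation provided they fit inclusion and exclusion criteria". Under Patient characteristics, frailty is one of the measures completed at baseline.

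On power, the Sample size section says that 160 per group "provides adequate power for subgroup analysis for the primary outcome if proportions are 40% or more". It gives no expected share for either subgroup and does not name the test.

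**The concern.** A subgroup factor should place every randomised participant in exactly one level. The age factor does. The frailty factor names two levels that are both degrees of frailty, in a trial that does not require frailty.

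An analyst following the text has two options. One is to leave non-frail participants out of the interaction model. The other is to put them in the 'frail' level under a rule the article does not state. These answer different questions, on different numbers of people, and the choice could be made after the frailty distribution is known. Neither gives the comparison many readers would look for, which is whether the effect on medication number differs between older people who are frail and those who are not.

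The power sentence adds a second ambiguity. Adequate power for an effect within a subgroup is easier to reach than adequate power for a difference between subgroups, and the planned analysis is the second.

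**Working it through.** **Step 1. Coverage of the levels.**

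| Factor | Levels named | Entry rule | Everyone placed? |
|---|---|---|---|
| Age | under 85; 85 and over | 70 and over | Yes |
| Frailty | frail; severely frail | none on frailty | No: not-frail has no level |

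**Step 2. The plan's own figures.** Inputs from the Sample size section: difference 2 medications, SD 2.5 (the SD of the reduction in the feasibility study, and the only SD given), 80% power, 5% significance. The analysis section makes tests two-sided.

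- n per group = 2 × SD² × (1.96 + 0.8416)² / difference² = 2 × 6.25 × 7.849 / 4 = 24.5, so 25. The stated 160 is not reproduced; it would need an SD of (2 / 2.8016) × √80 = 6.4.
- Attrition: 160 / 0.9 = 178, which agrees with the rounded 180.
- A 40% share of 160 is 64 per arm. Within that subgroup, SE = 2.5 × √(2/64) = 0.442, and power for 2 medications is Φ(2/0.442 − 1.96) = 0.995.
- At SD 2.5, a share of 25/160 = 16% already gives 80% within-subgroup power. The 40% condition therefore does not follow from SD 2.5. It would match a within-subgroup test at SD 4 (63 per arm, or 64 by t-test), an SD the article does not state.

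**Step 3. The planned interaction test.** With n1 and n2 the per-arm sizes of the two levels and n1 + n2 = 160:

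SE = SD × √(2/n1 + 2/n2); detectable interaction at 80% power = 2.8016 × SE; power for an interaction of 2 = Φ(2/SE − 1.96).

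| Split (assumed) | n1, n2 per arm | SE | Detectable interaction | Power for 2 |
|---|---|---|---|---|
| 40/60 | 64, 96 | 0.571 | 1.60 | 0.94 |
| 20/80 | 32, 128 | 0.699 | 1.96 | 0.82 |
| 15/85 | 24, 136 | 0.783 | 2.19 | 0.72 |
| 10/90 | 16, 144 | 0.932 | 2.61 | 0.57 |

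The detectable interaction scales with the SD. At SD 4 and a 40/60 split it is 2.56, and power for 2 is 0.59.

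**Step 4. What the missing level does to the frailty contrast.** Assume non-frail participants are left out and 40% of the rest are severely frail, with SD 2.5. No share is given in the article.

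| Non-frail share (assumed) | Severely frail, frail per arm | SE | Detectable interaction | Power for 2 |
|---|---|---|---|---|
| 30% | 44.8, 67.2 | 0.682 | 1.91 | 0.84 |
| 50% | 32, 48 | 0.807 | 2.26 | 0.70 |
| 70% | 19.2, 28.8 | 1.042 | 2.92 | 0.48 |

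The two readings can be compared in the 50% row. Leaving the non-frail out contrasts 32 with 48 per arm (detectable 2.26). Merging them into 'frail' contrasts the same 32 with 128 per arm (detectable 1.96). The merged contrast is more precise, but it sets the severely frail against everyone else.

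**The case against.** The article does not say that non-frail participants are excluded. It bases the grouping on an instrument that is not at hand, and a full protocol or analysis plan may give the cut-offs and a rule for other scores. That stands against asserting that participants will be lost. It does not remove the gap, because the article itself fixes the two levels and they do not cover the people it admits.

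The tests are exploratory, and estimates with 95% confidence intervals are already planned for outcomes in general. That stands, and it limits the consequence.

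A reader might go further on four points that the document does not support.

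- *That the 40% share will not be met for age 85 and over.* The power sentence is openly conditional, and no age distribution is given. On the stated SD, about 16% suffices within a subgroup and about 20% for an interaction of 2.
- *That the test can detect only interactions as large as the target effect of 2.* At 40/60 the figure is 1.60 and at 20/80 it is 1.96, both below 2. An interaction of 1 medication has 42% power at 40/60, but the article names no such benchmark.
- *That frailty must be worse powered than age.* This holds only at equal splits. With 30% non-frail left out and 40% of the rest severely frail, the detectable interaction of 1.91 is smaller than the 1.96 for age at 20/80.
- *That a null interaction will be reported as proof of equal effect.* The article states an expectation of no significant interaction. It does not say that non-significance will be taken as equivalence.

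Replacing categories with continuous modifiers is an option, not a requirement. Complete categories tested by an interaction term are legitimate.

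**Conclusion.** The frailty factor is incomplete as written: the entry rule admits non-frail people and the two named levels do not include them. This rests on the text alone and needs no assumption about shares. How many participants are affected cannot be known from the article. The frailty analysis as specified cannot compare frail with non-frail people.

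The power sentence is ambiguous rather than shown to be wrong, since it does not say that it refers to the interaction test planned later. At SD 2.5 and 160 per arm, the interaction detectable with 80% power is about 1.6 medications at 40/60 and about 2.0 at 20/80. These figures depend on assumed splits and on an SD that does not reproduce the stated 160 per group; a larger SD raises them in proportion.

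The interaction tests are exploratory, so neither the primary comparison nor its conclusion is affected. The change is worth making because it is simple and removes a choice that could otherwise be made after the data are seen.

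**What to change.** 1. Define frailty so that every randomised participant is included: not frail, frail and severely frail, with the score cut-offs stated. If a level may be sparse, state the rule for combining levels in advance. The baseline frailty score may be used as a continuous modifier instead, or alongside.
2. Report each interaction as an estimate with its 95% CI, and state that a non-significant result will not be read as equal effect. Reword the no-interaction hypothesis to match.
3. In the Sample size section, say whether the subgroup sentence concerns the effect within a subgroup or the interaction. For the interaction, give the detectable size with the SD and split assumed, for example about 1.6 medications at 40/60 with SD 2.5.

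The cost is analysis wording only. Frailty and age are already collected at baseline, so no new data, visits or participants are needed. The wording should be settled while the analysts are still blinded, and recorded through the route the article already gives for protocol changes.

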### Qualitative data analysis

As some decisions are often emergent in qualitative research, we provide only brief details of our analytic approach to the qualitative piece to the study. Pseudonyms will be assigned to participants. Audiotapes for interviews will be transcribed verbatim. The transcripts will be coded inductively and independently by two research team members in three stages: open, axial, and selective [76]. The interview data generated (with patients, pharmacists, and family physicians), family physician and pharmacist field notes, and patient diaries will be analyzed using thematic analysis to identify, analyze, and report patterns in the data. Dedoose, an online data analysis application for qualitative and mixed methods research [77], will be used to support analysis. Consistent with recommendations, two strategies will be used to foster trustworthiness [78, 79]. First, two coders will independently code 100% of the data and meet to discuss initial patterns and themes and explore disagreement. Second, authenticity will be maintained by displaying direct quotations within the results.

### Adherence and fidelity issues

Adherence will not affect the ability to measure the main study outcomes in the way it does in other trials as it is part of the outcome measure itself. The need to restart medications is not seen as a protocol violation or bias, nor is it seen as a failure of treatment, rather it is seen as effective monitoring during the “pause and monitor” phase. Fidelity to the intervention will however be assessed using a checklist of critical elements (see Additional File 6).

### Contamination

Access to TaperMD is by individual record unique ID. Pharmacists and physicians will only be able to access TaperMD intervention patients. Access will only be available for control patients after they have passed through the 6-month data collection point.

### Loss to follow-up

We conservatively anticipate the loss to follow-up rate to be a maximum of 10%. Our experience in a discontinuation RCT of antidepressants in primary care showed only a 4% loss to follow-up over 18 months [80], and our feasibility studies in the same age group showed a loss to follow-up of less than 8%. Our TAPER feasibility RCT showed loss to follow-up of only 3 patients. We found regular contact, multiple alternate contact details, and a measured informed consent process, particularly ensuring participants are clearly able to be available for follow-up, are helpful in minimizing such losses. In our feasibility study, we found it unhelpful to recruit participants during the “snowbird” period in winter who were traveling outside of Canada for an extended time as many older Canadians do. Perceived insurance restrictions mean they are not willing to change their medication in the period prior to leaving. The participants lost to follow-up will be classified as lost to follow-up due to an inability to contact, elected to no longer be part of any further follow-up (withdrawal of consent), or unable to participate because of ill health. In cases where participants who are lost to follow-up do not explicitly withdraw consent, medication and health care utilization data will still be collected from patient charts via chart audit where possible.

### Safety and monitoring

Details of any clinically adverse symptoms or effects reported to researchers at research data collection points will be securely provided to their family physician and pharmacist at that time, either by personal communication from the research team or electronically to a secure clinic fax number as appropriate. These processes did not compromise the blinding in our feasibility study [42]. Any such adverse effects will be addressed within the usual primary care clinical setting by their family physician who will be responsible for the clinical follow-up medication pause or dose reduction. Clinical follow-up will occur as determined by the monitoring requirements for the particular drugs discontinued.

If the patient experiences a serious adverse event (SAE), defined in a previous section on adverse events, a local SAE record will be completed and reported to the family physician within 24 h if they are unaware. The study team will notify the research ethics board of any SAE thought to be related to the study, using the standard SAE form. The form will be signed off by the principal investigator within 48 h. No formal auditing of trial conduct will take place. There will not be a data monitoring committee involved with the trial as there are no stopping rules for the trial and no planned interim analyses. Research staff will be responsible for overseeing study progress. Regular contact among study team members and clinic staff will be made to discuss and resolve any issues thought to be related to study conduct, and if any protocol or process changes are required these will be recorded as previously stated. There are no provisions for post-trial or ancillary care, as patients will continue to receive care as necessary from their physician throughout and following participation the trial. Furthermore, the study is low-risk and no harms from trial participation are anticipated.

### Dissemination policy

All results of the trial will be published, and there are no publication restrictions.

## Discussion

This study protocol describes an RCT designed to assess the effect of TAPER in reducing polypharmacy. Polypharmacy is associated with negative health outcomes. It is not known whether these effects are reversible if polypharmacy is reduced. The study is designed to assess the effect of TAPER on reducing polypharmacy and the extent to which this affects selected health outcomes, based on the negative associations with polypharmacy found in non-randomized studies. This study will be a large multi-centered single-blinded RCT.

Our study so far is unique in its design in aiming to introduce an operationalized structured clinical pathway aimed to tackle polypharmacy in a primary care setting while at the same time recording patient’s goals and priorities for treatment. A variety of explicit tools and deprescribing guidelines are available to flag medications that may be inappropriate or suitable for discontinuation in older adults. In addition, there are several studies evaluating pharmacist and physician collaboration to improve medication management in primary care [18]. However, very few pathways integrate all of these in one place and across all medications simultaneously, and fewer operationalize patients’ views and consideration of patients’ actual goals and priorities for treatment.

A strength of this trial design is its pragmatic nature and the setting where the evidence will be applied. The pathway and tool are immediately scalable and the results of the trial, if successful, will be directly translatable into clinical practice. Evidence from this study will help understand the provision of a systematic approach to considering reduction of the burden of polypharmacy, as well as providing a systematic clinical pathway for implementation including integration of available evidence tools, active monitoring, and reinstatement criteria.

While there are many studies associating negative health outcomes with polypharmacy, these result in observational data only and do not prove that outcomes improve when polypharmacy is reduced. If successful, our aim in testing this intervention is to lay the foundation for this model to be incorporated and become a part of routine preventive care in older adults.

## Trial status

Recruitment for the trial started in June, 2018, and is expected to continue recruitment until late 2021. This is protocol version 1, July 31, 2020.

## Data Availability

The study team will have full access to the dataset. Data will be made available once planned analyses and publications by the study team are completed, as well as online training materials. Anonymized patient-level data will be made available for meta-analyses on request. There are no plans to grant access to statistical code.

## Abbreviations

API: Application programming interface
CTCAE: Common Terminology Criteria for Adverse Events
EMR: Electronic medical records
ITT: Intention-to-treat
LOCF: Last-Observation-Carried-Forward
MAR: Missing at random
MI: Multiple imputation
MMSE: Mini-Mental Status Examination
MNASF: Mini-Nutritional Assessment Short-Form
PEI: Patient Enablement Instrument
PIM: Potentially inappropriate medication
RCT: Randomized controlled trial
REDCap: Research Electronic Data Capture
SAE: Serious adverse event
SEAMS: Self-Efficacy for Appropriate Medication Use scale
STOPP: Screening Tool of Older Person’s Prescriptions
TAPER: Team Approach to Polypharmacy Evaluation and Reduction
QALY: Quality-adjusted life years
